**Figure 1 F1:**
[figure not shown]
Overview of the web-based intervention. The web-based intervention (control as well as experimental) comprises six modules. Each module consists of four sessions (S). The participants can freely decide when they will work on the session. The next session becomes unlocked, when (1) 1 week has past since last session was completed and (2) all guided-tasks are successfully completed. Thus, participants are able to finish each module within 4 weeks (1 month).

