#### 2.3.1. Motivation Module

Ward et al. name offender's motivation to change and the resulting involvement in therapy as an intermediate target to be addressed before criminogenic needs can be changed (51). A study surveying ISAC showed a positive impact of motivation for treatment on therapy success (52). In a web-based program for the treatment of alcoholism, motivation to change correlated with dropout out of the program as well (53). Furthermore, Melville et al. illustrated in a review article that most patients who abort a web-based intervention do so before the actual treatment begins (54). Van Ballegoojen et al. come to a similar conclusion, adding that regarding the point in time at which treatment is abandoned, there is little difference between outpatient therapies and web-based therapist-guided treatment (55). As it is reasonable to expect that for convicted ISAC and ICCSEM under CS, motivation to change has an effect on treatment progress, -success and dropout too (52, 56), this underlines the necessity of working on participant's motivation at the beginning of the planned study. The motivation module makes use of motivational interviewing techniques (50). They are based on the assumption that people are ambivalent about changing their behavior. The therapist should support the patient in finding both reasons for and against changing their behavior, thus allowing the patient to naturally develop a desire to change. Accordingly, working with values and goals is a central aspect of motivational interviewing. The four principles underlying this process are (1) express empathy, (2) develop discrepancy, (3) avoid arguments, and (4) support self-efficacy. The methods used to implement these principles are (1) asking open questions, (2) reflective listening, (3) appreciating statements, (4) methods supporting change talk, (5) methods dealing with resistance, (6) methods supporting confidence talk, and (7) summaries.

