
### 2.4. The Placebo Web-Based Intervention (Placebo Condition)

The control condition is a placebo web-based intervention with the same mode, dose, and amount of support and attention by supporting online coaches as in the experimental condition—but the content of the modules is unrelated to the proposed dynamic risk factors. The content of the placebo condition comprises information on healthy living, e.g., healthy nutrition, physical activities, or healthy sleep. The amount of exercises is the same as in the experimental condition but exercises are specifically designed to not induce any sustainable effect.

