### 2.6. Procedure

The clinical trial starts on January 01, 2021 and ends on December 31, 2022. All potential participants are screened by their SO based on inclusion criteria and the SO hands out written information on the trial. If the potential participant is generally interested in participating, an individual meeting with an independent research assistant will take place at the supervision office. During this meeting, the research assistant provides detailed information about the goals and procedure of the trial, data security and advantages or disadvantages of taking part in the trial. If the potential participant is further interested to take part, he or she will receive an information letter, the informed consent, an intervention agreement, and a letter releasing the SO from the confidentiality obligation. In the intervention agreement, the participant agrees not to commit offenses during the participation and is informed that any violation will lead to exclusion. Furthermore, the research assistant performs the pre-intervention assessments (see Supplementary Table 1). If a potential participant does not want to take part in the trial, he or she will be asked for informed consent in filling out one questionnaire (QNP) and to allow to fill out the SSQ-CF checklist by the research assistant as well as the SSQ-SO by the SO. Further, the potential participant is asked for allowance to assess his or her officially registered re-offenses in a 5-years follow up in order to be able to control for a potential volunteer-effect. After obtaining the written informed consent, the intervention agreement, and the release from confidentiality, the participant is randomly allocated to the experimental or the control condition. The username as well as the initial password is delivered by post to the SO, who will give it to the participant. After the first log-in, the participant has to change the initial password due to security reasons. After changing the initial password, the participant has to go through an introduction, which explains the usage of the intervention website, before he or she can start with the first online module. The procedure for the placebo condition is the same as for the experimental condition, only the provided online contents differ. In both the placebo and the intervention condition, the provided content is divided into six online modules. Each module is further divided into four sessions. Each session has a duration of about 60 min and the participant is advised to finish one session per week. Consequently, the intervention as well as placebo consists of 24 sessions which can be completed in 24 weeks. The participant will be reminded by in-app messages or by the SO if he or she is late in finishing the next session. During both online conditions, data of primary outcome (IoD) is assessed at 7 measurement time-points. Except questionnaires which are filled out at clearing up all questionnaires are provided online within the web-based app. This ensures that the questionnaires are filled in at the predefined measurement time-points. Five years after the last patient out, re-offenses are assessed by officially documented re-offenses (see Supplementary Table 1 for an overview on measurement time-points).

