### 2.10. Power and Sample Size Calculations

It is assumed that participants who take part in the experimental treatment show significantly lower values of self-reported dynamic risk factors inter-, and post-treatment controlling for baseline values as well as less officially recorded re-offenses in a 5-years follow-up, compared to the placebo condition. Within programs for individuals who have sexually offended, higher levels of motivation and better treatment engagement were associated with decreased attrition (128). The study design addresses this in a direct manner by providing an online motivation module at the beginning of the intervention. A rate of 50% of screened participants taking voluntarily part in the clinical trial is assumed. Based on the estimation of the ministry of Lower-Saxony and Baden-Wuerttemberg, it is expected to see 1,165 subjects eligible for participation during the recruitment period of which 50% (*N* = 582) are expected to participate in the study. Taking a dropout of 26.4% (128) into account, it is expected to see *N* = 428 subjects completing the web-based intervention or placebo intervention. With *N* = 214 subjects in both conditions (treatment and placebo) it is possible to detect small effects (*d* = 0.27) with a power of 80% at a significance level α = 5%. This effect size is in the expected range based on the above shown literature.

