### 2.11. Statistical Analysis

All patients who discontinue from the study are identified and the extent of their participation in the study is reported. If discontinuation is due to clear evidence for recidivism or concrete preparation for or intention to recidivism (assessed by responsible SO or guiding therapist) the subject receives the maximal value for self-reported dynamic risk factors for the remaining measurements (assuming the worst case of a failed treatment). In all other cases of drop-out, the reason is recorded. The efficacy of the web-based intervention based on the first primary outcome measure (IoD) will be analyzed by means of Gaussian linear model for repeated measures (MMRM) with treatment group, time (six time-points; after each web-based intervention module (see Supplementary Table 1); treatment-by-time interaction, and the randomization strata as factors (offense type, type of CS, external treatment in addition to CSaU), and baseline measurements (at clearing up) of the outcome as co-variate. The error terms are assumed to follow a multivariate normal distribution with unstructured co-variance. Least squares mean changes from baseline are reported for the treatment groups with 95% confidence interval (CI) as well as the difference between the least squares treatment group means with 95% CI and *p*-value testing the null hypothesis of no treatment effect. The analysis is performed on the Intention-To-Treat (ITT) population comprising all patients who have completed at least one module. The second primary outcome measure (officially recorded re-offenses) will be analyzed by means of Cox proportional hazard model with treatment group, number of completed modules and the randomization strata (offense type, type of CS, external treatment in addition to CSaU, risk to re-offend at baseline). The effect of each module will additionally be analyzed using the Wilcoxon signed rank test for paired data comparing the pre- and post-module scores, adjusting the *p*-values using the Bonferroni-Holm's method to control the family-wise error rate. Economic analyses will be based on analytic modeling techniques. Data will be derived from the clinical trial (e.g., recidivism rates based on dynamic risk factors), the literature (e.g., tangible benefits), and experimental procedures (e.g., contingent valuation/revealed preference approaches to assess intangible benefits). Results of the analysis will be presented in terms of net benefit (NB) estimates and a benefit-cost ratios. The NB will be calculated as NB = tangible benefits + intangible benefits-intervention costs. The intervention will be considered cost-beneficial relative to the control condition if the NB is positive and the benefit-cost ratio exceeds 1.00 following standard economic decision rules. Since many cost parameters associated with ISAC and ICCSEM occur after the trial period, the cost-benefit of the intervention will be modeled for a 5-years period. Sensitivity analyses will be conducted to examine how the NB will be influenced by variations in model parameters.

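### The population labelled ITT for the primary IoD analysis is a post-randomisation, completion-based set, and it drops participants removed for recidivism during module 1

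*Protocol article*

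**What the plan says.** Section 2.11 of the protocol article describes the IoD model: repeated measures at six time-points, one after each module, with the baseline score as covariate. It closes that description with "The analysis is performed on the Intention-To-Treat (ITT) population comprising all patients who have completed at least one module". The Cox model for re-offences comes next, and no population is named for it.

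Section 2.6 gives the order of events. Once consent and the agreements are in hand, "the participant is randomly allocated to the experimental or the control condition". Log-in details are then sent, the password is changed, and the participant goes through an introduction "before he or she can start with the first online module".

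On the content of module 1, Section 2.10 discusses attrition and says: "The study design addresses this in a direct manner by providing an online motivation module at the beginning of the intervention". Section 2.3.1 cites a review in which "most patients who abort a web-based intervention do so before the actual treatment begins". Section 2.4 says of the placebo arm that "the content of the modules is unrelated to the proposed dynamic risk factors".

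On discontinuation because of recidivism, or of preparation for or intention to it, Section 2.11 says that "the subject receives the maximal value for self-reported dynamic risk factors for the remaining measurements".

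**The concern.** Intention-to-treat protects the comparison because membership of the analysis set is settled at randomisation. Here membership is settled weeks later, by whether module 1 was finished. That event can depend on what the arm delivers, and the protocol intends experimental module 1 to influence retention. If the arms keep different kinds of participants, the compared groups are no longer the randomised ones, and a larger sample does not cure that.

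The set definition also meets the worst-case rule awkwardly. Someone removed for recidivism during module 1 is scored as a complete failure by one sentence and left out of the analysis by another. Following both as written drops the earliest outcome-related failures from a comparison labelled ITT.

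**Working it through.** **1. Timing.** Allocation comes first, then log-in, introduction and module 1 (Section 2.6). Under the Figure 1 legend a session opens one week after the previous one was completed. Four sessions therefore involve three waits, so a module takes roughly three to four weeks at the advised pace. Everyone excluded by the one-module rule has already been randomised.

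**2. The plan's sample size.** Inputs from Section 2.10: 1,165 eligible, 50% participation, 26.4% dropout, d = 0.27, power 80%, alpha 5%.
- 1,165 × 0.5 = 582.5, stated as 582.
- 582 × (1 − 0.264) = 428.4, so 428, or 214 per arm.
- n per arm = 2 × (1.960 + 0.842)² / 0.27² = 216 (two-sided). Power at 214 per arm is 79.8%.

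The figure reproduces and is not in dispute.

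**3. How many would be excluded.** The article gives no dropout rate for module 1. By assumption: 5% of 582 is 29, 10% is 58, 20% is 116. The extreme, with all 26.4% falling in module 1, is 154.

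**4. Illustrative bias in IoD with no true effect.** Suppose an arm loses a share p before module 1 ends, and those lost are s SD worse than the arm's overall mean. The retained mean is then better by p × s / (1 − p). With assumed losses of 10% (experimental) and 16% (placebo):
- s = 0.3: 0.16 × 0.3/0.84 − 0.10 × 0.3/0.90 = 0.057 − 0.033 = 0.024 SD.
- s = 0.5: 0.095 − 0.056 = 0.040 SD.

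That is 9% to 15% of d = 0.27. In this set-up the retained placebo group looks better, so the error runs against the intervention. Swapping the two losses reverses the sign.

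**5. A second selection model.** Let completion depend on a normal propensity that correlates rho with outcome. With completion share c, the retained mean shifts by rho × φ(z)/c, where φ is the normal density and z the cut-off that leaves a share c. Completion shares and rho (0.2 to 0.5) are assumptions; 291 per arm are randomised.

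| Completion by arm | Spurious difference (SD) | Two-sided type I error |
|---|---|---|
| 90% vs 85% | 0.016–0.040 | 5.4–7.3% |
| 90% vs 80% | 0.031–0.077 | 6.4–13.8% |
| 95% vs 85% | 0.033–0.083 | 6.7–15.7% |
| equal | 0 | 5% |

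**6. Removals during module 1.** All six IoD time-points lie after such a removal, so the worst-case rule would fill all six. The set definition discards all six. The article gives neither the expected number of such removals nor the IoD maximum in SD units, so this part cannot be sized.

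**7. Power with all randomised.** At 291 per arm and undiluted d = 0.27, power is 90.3%. If a share f of participants has no effect, the detectable mean is 0.27 × (1 − f). Power is then 87.2% (f = 5%), 83.4% (10%), 79.1% (15%), 74.1% (20%) and 66.9% (26.4%). These values treat every participant as contributing an outcome; imputation uncertainty would lower them.

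**The case against.** The strongest reply is that the rule changes little in practice. The first post-baseline IoD in the model comes after module 1 and baseline is a covariate, so an ordinary module-1 leaver has no response to contribute whatever the set is called. This stands for ordinary leavers: most of the potential bias comes from missing outcomes, and a new label alone would not remove it. It does not stand for recidivism removals, because the plan itself supplies their values.

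A second reply is that the two sentences are compatible if the maximal value is applied only within the analysed set. That is a coherent reading, so they are not strictly incompatible. But the rule is justified as assuming the worst case of a failed treatment, and on this reading the earliest failures escape it. The text has to say which applies.

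Third, the arms are matched on mode, dose and support (Section 2.4) and participants are blinded (Section 2.8), which works against differential dropout. This also stands: differing completion is something the design could produce, not something the article shows.

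Fourth, Section 2.11 promises to identify everyone who discontinues and to report how far they took part. They would therefore be visible in the report, though absent from the estimate.

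Finally, an article condenses a fuller protocol. That excuses silence, but here the population is defined explicitly, and the definition is not ITT.

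**Conclusion.** The population for the primary IoD analysis is wrongly labelled and should be corrected. It is selected after randomisation by completion of a module that differs between arms, and it discards recidivism removals during module 1 that the plan elsewhere scores as failures. Any bias is of unknown size and direction: about 0.02 to 0.04 SD under the assumed 10% and 16% losses, up to 0.083 SD in the less favourable scenarios tried, and none in the selection model if completion is equal.

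A reader might infer more than the article supports:
- **That both primary analyses are affected.** The sentence closes the IoD description and does not clearly extend to the Cox model. The number of completed modules, a term in that model, can also be zero. No bias figure for re-offences is warranted.
- **That completion does depend on arm.** Only the intention behind the motivation module is documented.
- **That more than 77 participants would be lost,** as half of 0.264 × 582 = 154. This multiplies a dropout rate from one source by a remark from another, and leaving before treatment begins is not the same as leaving before module 1 is finished.

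**What to change.** - Define ITT as all randomised participants, analysed by allocated arm.
- For IoD, apply the plan's own worst-case value from randomisation onward, including removals during module 1, so that the two sentences of Section 2.11 agree.
- Include non-starters and other module-1 leavers through a stated missing-data method, for example multiple imputation, with a sensitivity analysis on its assumption.
- State that the re-offence analysis uses all randomised participants whose records can be obtained, whatever their module completion.
- Rename the present set as those who completed at least one module and keep it as a sensitivity analysis.

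The cost is wording, one explicit missing-data assumption and possible dilution of the effect estimate. Under the simplification in step 7, power stays above 80% if 10% of participants have no effect and falls just below it at 15%.

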##### 2.5.1.1. Officially recorded re-offenses

Officially recorded re-offenses in the experimental condition compared to the placebo condition are the first primary outcome. Officially recorded re-offenses are obtained 5 years after last patient out.

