
### 2.12. Stopping Rules

The individual subject is excluded from the clinical trial if the responsible SO or the online coach reports clear evidence for sexual recidivism or concrete preparations for any sexual recidivism. The clinical trial is stopped if an interim analysis at the mid-point of the project (12 months after first patient in; tested on subjects having completed at least two modules of the web-based intervention) demonstrates: (a) a significantly higher risk to re-offend (based on main outcome and number of reported significant events in the experimental condition compared to the placebo condition); (b) a significantly higher proportion of reported significant events (see a) in the experimental condition than in the placebo condition; (c) a significantly increased proportion of high-risk subjects (defined in terms of the main outcome) compared to the proportion at baseline.

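### The only Cox model stated for re-offences adjusts for modules completed after randomisation, so its hazard ratio does not estimate the randomised effect and can be biased either way if completion differs by arm

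*Protocol article*

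**What the plan says.** Section 2.5.1.1 sets the contrast: "Officially recorded re-offenses in the experimental condition compared to the placebo condition are the first primary outcome". Section 2.11 numbers this outcome second rather than first, but it is primary in both places. Section 2.11 then states the analysis: re-offences "will be analyzed by means of Cox proportional hazard model with treatment group, number of completed modules and the randomization strata", the strata being offence type, type of supervision, external treatment and baseline risk. The module count is listed as an ordinary covariate. It is not described as time-dependent, as an interaction with arm, or as part of a supplementary analysis.

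Four other places bear on that covariate:

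- Timing. In section 2.6 participants are randomised before first log-in, and "the intervention as well as placebo consists of 24 sessions which can be completed in 24 weeks".
- Exclusion for offending. In the intervention agreement (section 2.6) "the participant agrees not to commit offenses during the participation and is informed that any violation will lead to exclusion". Section 2.12 adds: "The individual subject is excluded from the clinical trial if the responsible SO or the online coach reports clear evidence for sexual recidivism".
- Motivation and attrition. Section 2.3.1 expects that "motivation to change has an effect on treatment progress, -success and dropout too". Section 2.10 says of attrition: "The study design addresses this in a direct manner by providing an online motivation module at the beginning of the intervention".
- Placebo content. Section 2.4 says "the content of the modules is unrelated to the proposed dynamic risk factors".

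**The concern.** A covariate in the primary model of a randomised trial should be fixed before allocation. The module count is not, and three features make it a poor thing to condition on.

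1. Arm may change it. Only the experimental content works on motivation, and the protocol links motivation to drop-out.
2. The outcome can change it. A participant whose re-offending is detected during the programme is excluded and completes no further modules. Entering the final count as a fixed covariate also lets the hazard early in follow-up depend on information that arises later.
3. It shares causes with the outcome. Motivation is expected to influence progress, success and drop-out alike. Conditioning on a variable that both arm and prognosis affect can create an association between arm and prognosis that randomisation had removed.

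The count also measures exposure to the intervention, so any benefit gained by completing more modules would be adjusted away. At stake is whether the reported hazard ratio answers the question in sections 1.3 and 2.5.1.1: whether people assigned to the intervention re-offend less than people assigned to placebo.

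**Working it through.** **Inputs from the protocol.** 1,165 eligible, 50% participation, N = 582, drop-out 26.4%, 214 completers per condition, d = 0.27, 80% power, alpha 5% (2.10); 1:1 allocation (2.7); six modules of about one month each (Figure 1 caption); re-offences obtained five years after last patient out (2.5.1.1); published re-offence rates of about 6%, and 18% versus 20% (1.1).

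**Assumptions not in the protocol.** One normal latent trait U (risk and low motivation) with log-hazard coefficient 1 on both drop-out and re-offending; treatment multiplies the drop-out hazard by 0.5, 1 or 2; five-year control re-offence parameter 20% or 6%; 66 months of follow-up; module count cut at re-offence. Strata were not simulated.

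**Step 1: the plan's own figure.** 1,165 × 0.50 = 582.5. 582 × (1 − 0.264) = 428.4, or 214 per arm. Power = Φ(0.27 × √(214/2) − 1.96) = Φ(2.793 − 1.960) = Φ(0.833) = 79.8%, which reproduces the stated 80% (two-sided). It concerns a mean difference. No hazard ratio or event count is given for the Cox analysis. Its relevance here is that it plans equal completion in both arms.

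**Step 2: the model.** Monthly re-offence hazard = λ₀ · exp(βA + U − ½), with λ₀ = −ln(0.80)/60 = 0.00372 or −ln(0.94)/60 = 0.00103. Drop-out hazard per module = [−ln(1 − 0.264)/6 = 0.0511] · exp(δA + U − ½), with δ = ln 0.5, 0 or ln 2. The count is the smallest of six, the whole modules before drop-out, and the whole months before re-offence. Cox models were fitted with and without the count, on 400,000 subjects per scenario.

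| Truth, five-year parameter | Arm's effect on drop-out | Mean modules, placebo / experimental | HR without count | HR with count |
|---|---|---|---|---|
| Null, 20% | halves | 5.10 / 5.46 | 1.017 | 1.157 |
| Null, 20% | none | 5.10 / 5.10 | 1.006 | 1.005 |
| Null, 20% | doubles | 5.10 / 4.51 | 0.992 | 0.833 |
| Direct HR 0.70, 20% | halves | 5.10 / 5.49 | 0.728 | 0.826 |
| Direct HR 0.70, 20% | none | 5.09 / 5.11 | 0.723 | 0.718 |
| Direct HR 0.70, 20% | doubles | 5.09 / 4.52 | 0.732 | 0.611 |
| Log-hazard lower by 0.06 per module, 20% | halves | 5.10 / 5.49 | 0.758 | 0.876 |
| Null, 6% | halves | 5.14 / 5.51 | 0.990 | 1.134 |
| Null, 6% | doubles | 5.13 / 4.54 | 0.979 | 0.821 |

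Read across each row, since both fits use the same simulated data and so share simulation error. In the 0.70 rows the unadjusted value is 0.72 to 0.73 because the latent trait is left out of the model.

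**Step 3: which mechanism matters.** With truncation only (no shared cause, equal completion) a hazard ratio of 0.70 is unchanged: 0.701 and 0.701. With drop-out halved but no shared cause, the null moves from 0.995 to 1.048. With both, it moves from 1.017 to 1.157. In these runs a difference in completion between arms was needed, and the shared cause enlarged the shift. Restricting to participants with at least one completed module gave 1.156 and 0.822 in the halved and doubled null scenarios at 20%, so that restriction does not remove it.

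**Step 4: type I error at N = 582, 20% parameter, 1,500 simulated trials each (nominal 5%).** For drop-out halved / unchanged / doubled: with the count 12.5% / 4.5% / 13.2%; without it 5.7% / 3.8% / 4.9%.

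**Step 5: the same at 6%, by approximation.** Events = 582 × 0.06 = 34.9, so SE(log HR) ≈ 2/√34.9 = 0.34. Shifts are ln(1.134/0.990) = 0.136 and ln(0.821/0.979) = −0.176, or 0.40 and 0.52 SE. Rejection ≈ Φ(−1.56) + Φ(−2.36) ≈ 7% and Φ(−1.44) + Φ(−2.48) ≈ 8%. With few events the distortion is harder to see in the test, but the hazard ratio is shifted as much.

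**The case against.** The strongest reply is that the plan itself expects equal completion. It uses one drop-out rate and 214 completers in each condition, and section 2.4 gives placebo the same mode, dose and coach support. With equal completion the simulated hazard ratio does not move, even with the shared cause and the truncation switched on. Halving or doubling the drop-out hazard is a large contrast that nothing in the protocol predicts.

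The link from outcome to covariate is also looser than it first appears. Exclusion follows evidence held by the supervision officer or coach, whereas the outcome is an officially recorded offence, and section 1.1 notes delayed registration and undetected acts. If modules take about 6 of 66 months, only about 6/66 = 9% of events at a constant hazard fall in the window where they could truncate the count.

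All of this stands as a limit on size and sign. A reader might infer that the hazard ratio is certainly biased, or that a true benefit will be understated because the motivation module keeps participants in the programme. The documents do not support either inference. Section 2.10 presents the module as a response to attrition but predicts no difference between arms, and if the experimental arm completed fewer modules the error would favour treatment (0.611 against 0.732).

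The reply does not rescue the covariate. A primary test should not be valid only if completion happens to balance. Nor does the count serve as a dose adjustment: the dose is self-selected, the event can cut it short, and a single per-module coefficient treats active and placebo modules as equivalent.

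**Conclusion.** The point holds as wrong as written, with limited claims about magnitude. That the covariate is inappropriate follows from the protocol alone: it is measured after randomisation, it is in the only stated model for a primary outcome, and the resulting coefficient is not the contrast between randomised groups that the outcome definition sets. Whether and how far the estimate is biased depends on completion by arm, which is unknown at the planning stage.

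Under the assumptions listed, adding the count multiplies a null hazard ratio by about 1.157/1.017 = 1.14 if treatment halves drop-out and by about 0.833/0.992 = 0.84 if it doubles it, and by almost nothing if completion is equal. The type I error of about 13% belongs to the unequal-completion scenarios at the 20% rate; at 6% it is nearer 7 to 8%. A weaker shared cause or a smaller difference in completion would shrink all of these figures.

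**What to change.** In section 2.11, and in the analysis plan if it repeats the model, delete the module count from the primary Cox covariates. Keep treatment group and the four baseline randomisation factors, with participants analysed as randomised. If module completion is of interest, examine it in a separate analysis labelled exploratory and non-randomised, for example with completed modules as a time-dependent exposure, and draw no primary conclusion from it.

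The cost is one phrase. No extra data, participants or follow-up are needed, because the count is still recorded for the exploratory analysis. The change is best made before any re-offence data are seen by arm.
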